### Intervention measures

#### Surgical procedure

All surgeries will be performed by 1 designated surgeons from our center. These designated surgeons are required to undergo a meniscal surgical technique evaluation and register with the center before being permitted to participate in the study and perform surgeries. Arthroscopic surgery will be performed under general anesthesia. If repairable meniscal lesions are found in the patient, the lesions will be first cleared using a shaver for freshening. All patients will receive a full-endoscopic meniscal repair technique, and if the meniscus is not repairable, the partial meniscectomy can be performed to reshape the meniscus.

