## Aim of study

This study will recruit adult participants diagnosed with isolated longitudinal meniscus injuries confirmed through arthroscopic examination and scheduled for meniscus repair. The primary objective of this research is to assess the safety, effectiveness, and feasibility of implementing a digital rehabilitation program that incorporates computer vision and augmented reality as part of the postoperative rehabilitation process.

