## Methods

### Study design

This is a single-center, prospective, randomized controlled study. After receiving informed consent, participants will be randomly allocated into two groups: the experimental group and the control group will adopt the standardized rehabilitation protocol (Table 1). The experimental group will engage in a digital rehabilitation program that can be completed from home, whereas the control group will attend weekly physical therapy clinic sessions for exercise guidance. The flowchart of the study is shown in Fig. 1.

**Table 1 Tab1:** The standardized postoperative rehabilitation plan

Overall goal: Stage 1: 0–2 weeks: Control of swelling and symptoms after surgery, early progressive weight bearing, and ROM
Control of swelling and symptoms: (1) apply ice at least 3 times a day after surgery, 20 min each time; (2) apply the elastic bandage to compress the affected limb; (3) elevate the affected limb and lie flat on your back when sleeping and cushion a pillow with a certain thickness under the affected limb
ROM and brace use: (1) 0–60 degree fixation, early gentle knee movement under sitting position (2) heel support training, ensuring knee joint at 0 degrees
Weight bearing: The knee brace is secured in the fully extended knee position, and crutches are used to transition from no weight bearing to partial weight bearing as tolerated
Exercises: (1) sitting hamstring pull (2) ankle pump (3) quadriceps isometric training (4) straight leg elevation training (15–30 degrees) (5) hamstring isometric training
Overall goal: Stage 2:3–6 weeks: Early exercise and strength training, ROM, and partial weight bearing as tolerated
ROM and support use: (1) 3–4 weeks: 0–90-degree fixation, complete knee extension and bend to 90 degrees (2) 5–6 weeks 0–120-degree fixation, bend to 120 degrees
Weight bearing: With the knee brace fixed in the fully extended knee position, and using crutches, gradual weight bearing to full weight under tolerable conditions, and gradually remove of the crutches
Exercise: In addition to the training in the previous stage, include: (1) knee shin slide (2) supine straight leg raise 30 to 60 degrees (3) hip outreach training (4) lift heel stand (5) hip outreach (6) hip and (7) seat after knee flexion and stand
Overall goal: Stage 3: Weeks 7–12: Functional regression, gradual reduction of brace use, and restoration of total joint range of motion

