### Randomization

SPSS 23.0 (IBM, New York, NY, USA) will be used to generate random numbers. Subjects with odd numbers will be assigned to the experimental group, and subjects with even numbers will be assigned to the control group. The envelope method will be used for hidden grouping, which will be implemented by a third party. The random allocation scheme will be stored in an opaque envelope, which will be opened in succession according to the order of inclusion, thereby determining the assigned group for each patient. After that, the envelopes will be given to the study implementer, who will then use inclusion and exclusion criteria to decide whether each patient can be included in the study.

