### Subjects

Inclusion criteria:Isolated meniscus injury diagnosed by magnetic resonance imaging (MRI)Confirmation of a longitudinal tear pattern (including bucket handle tears) under arthroscopy, with a repairable tear.Suture meniscus repair with or without partial meniscectomyParticipants have sustained their meniscus injury due to physical activities, such as playing basketball.Willing to participate in this clinical trial and receive follow-up.

Exclusion criteria:Preoperative MRI diagnosis with other ligament or chondral lesions;A discoid meniscus was diagnosed under arthroscopy.Trauma and surgery to other weight-bearing joints in the lower extremities, such as torn ligaments in the ankle and necrosis of the femoral head in the hip, can indirectly affect knee load and movement.Knee osteoarthritis, defined by Kellgren–Lawrence grade II or higher or Outerbridge classification grade II and above. [19, 20]

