#### Postoperative rehabilitation protocol

A standardized postoperative rehabilitation protocol will be adopted according to the clinical guidelines in the American Academy of Orthopaedic Surgeons (AAOS) postoperative rehabilitation manual18 and previous studies1,2,4,14 (Table 1). [1, 2, 4, 18, 22]

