### Outcomes

#### Clinical knee function evaluation

The estimated follow-up time was 1 day before surgery and 2, 6, 12, and 24 weeks after surgery, and the specific evaluation items included knee ROM (2, 6, 12, 24 weeks after surgery), weight-bearing progress (when fully weight bearing) and knee function and pain scores [23] (Lysholm score, Tegner score, IKDC knee subjective function score, and VAS score). At the final follow-up assessment, return-to-play (RTP) status will be evaluated based on the rehabilitation literature available for meniscus repair. **(**Table 2**)**. [4, 24, 25]

**Table 2 Tab2:** Return-to-play assessment

VAS score = 0	
IKDC score > 90	
No active effusion (Brush test negative)	
The difference in circumference between the quadriceps muscles was less than 1.5 cm	
The knee isokinetic strength test showed a ratio of bilateral quadriceps muscles greater than 90%, bilateral hamstrings greater than 90%, and unilateral hamstrings to quadriceps muscle greater than 66%	
Jump test Limb symmetry index (LSI = jump distance on the affected side/jump distance on the healthy side *100%) was greater than 90%, and the test items included a single-leg long jump test and a single-leg triple jump test	
Y-word balance test: bilateral extension asymmetry within 4 cm; bilateral comprehensive score is greater than 90%	
Lateral step-down test showed no dynamic genu valgus	

The clinical function of patients was assessed and evaluated based on IKDC and VAS score improvement via the criteria of minimal clinically important difference (MCID), patient accepted symptom state (PASS), and significant clinical benefit (SCB) [25].According to the study of Gowd et al. [25], the MCID threshold, which represents the minimal clinically important difference, is defined as an improvement of at least 10.6 points in the IKDC score after treatment or intervention. This threshold signifies that a clinically meaningful change in knee joint function is recognized. The SCB threshold, indicating significant clinical benefit, is set at an IKDC score of 27.3 points or higher after treatment or intervention. This threshold is used to confirm that the treatment has brought about a significant clinical benefit. Lastly, the threshold for patient accepted symptom state (PASS) is established at an IKDC score of 57.9 points or higher. This threshold signifies that patients subjectively consider their symptom state to be acceptable.

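### The surgical section provides for partial meniscectomy when the meniscus is not repairable, entry requires a repaired tear, and allocation precedes the eligibility decision, so the trial status of such a patient is undefined

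*Protocol article*

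**What the plan says.** All references are to the Protocol article.

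- **Aim of study** describes the population as adults with "isolated longitudinal meniscus injuries confirmed through arthroscopic examination and scheduled for meniscus repair".
- **Subjects** makes this an entry criterion: "Confirmation of a longitudinal tear pattern (including bucket handle tears) under arthroscopy, with a repairable tear". A further criterion requires suture repair and permits partial meniscectomy alongside it.
- **Surgical procedure** states "All patients will receive a full-endoscopic meniscal repair technique", and the same sentence continues "if the meniscus is not repairable, the partial meniscectomy can be performed to reshape the meniscus". Nothing there says what becomes of that patient in the trial.
- **Study design** fixes the order of consent and allocation: "After receiving informed consent, participants will be randomly allocated into two groups".
- **Randomization** has the envelopes opened in sequence, which sets the group. They then pass to the study implementer, "who will then use inclusion and exclusion criteria to decide whether each patient can be included in the study".
- **Postoperative rehabilitation protocol** gives one plan for everyone: "A standardized postoperative rehabilitation protocol will be adopted". Table 1 has no branch by type of operation.
- **Clinical knee function evaluation** says that "return-to-play (RTP) status will be evaluated based on the rehabilitation literature available for meniscus repair".

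**The concern.** The trial compares two ways of delivering rehabilitation after meniscus repair, so the operation is meant to be the same in both arms. A patient who meets the entry criteria cannot have a non-repairable meniscus, yet the surgical section provides for one among all patients. The criterion that allows partial meniscectomy with a repair does not settle this. It covers resection added to a suture repair, not resection because repair was impossible.

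Repairability is known only at arthroscopy, while allocation is tied to consent and comes before the eligibility decision. The patient in question may therefore already have an arm. The article does not say whether that patient is then kept or removed, and each course has a cost:

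- **Kept:** the arms contain two operations, rehabilitated under one repair plan and judged for return to play by standards taken from repair.
- **Removed:** the exclusion happens after allocation and is decided by staff who hold the assignment. That opens the way to selection by arm and reduces the number analysed.

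**Working it through.** **1. The sections side by side.**

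| Question | Subjects | Surgical procedure | Study design and Randomization |
|---|---|---|---|
| Must the tear be repairable? | Yes, confirmed at arthroscopy | Provides for one that is not | Not addressed |
| Must a suture repair be done? | Yes; partial meniscectomy only in addition | All patients, then an exception | Not addressed |
| When is eligibility settled? | At arthroscopy | During the operation | After the envelope is opened |
| When is the arm fixed? | Not addressed | Not addressed | After consent, when the envelope is opened; not tied to the end of surgery |

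The first two rows conflict between Subjects and Surgical procedure. The last two leave room for a patient to be allocated and then found not to meet the criteria. No section says how that patient is counted.

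**2. The plan's own figures.** Sample size gives d = 0.8, α = 0.05, power 0.8, at least 26 per group, 20% loss and 32 recruited per group. A two-sample t-test (two-sided α assumed, since sidedness is not stated) needs n = 25.52, so 26 per group, with power 0.807. For loss, 26 × 1.2 = 31.2, rounded up to 32; 26/(1 − 0.2) = 32.5, rounded up to 33. The stated figures reproduce to within one patient per group, and this point does not dispute them.

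**3. Illustration of size.** The article gives no non-repairable share, so f is an assumption, shown over a range. Both scenarios start from 26 evaluable per arm.

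- Removed after allocation, over and above the 20% loss: n per arm = 26 × (1 − f), with d = 0.8.
- Kept, with no treatment difference in these patients and an unchanged SD (worst case): n = 26 per arm, with d = 0.8 × (1 − f).

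| f (assumed) | Removed: n per arm | Removed: power | Kept: d | Kept: power |
|---|---|---|---|---|
| 0 | 26 | 0.81 | 0.80 | 0.81 |
| 5% | 24.7 | 0.79 | 0.76 | 0.77 |
| 10% | 23.4 | 0.76 | 0.72 | 0.72 |
| 20% | 20.8 | 0.71 | 0.64 | 0.62 |
| 30% | 18.2 | 0.65 | 0.56 | 0.51 |

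The design starts barely above its 0.8 target, so even f = 5% takes it below. The table says nothing about which f applies.

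**The case against.** The best defence is that Subjects already settles eligibility. A patient who has only a partial meniscectomy fails two entry criteria, and the surgical section may simply describe what is done for someone who then drops out of consideration. It could also be read as trimming tissue that cannot be sutured, although the literal condition is that the meniscus is not repairable. Envelopes are opened in order of inclusion, which might suggest that eligibility has been checked by then. This defence stands to the extent that retention is not a stated plan. It does not close the gap. The article never says that such a patient leaves, and Randomization explicitly puts the eligibility decision after the envelope.

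A reader might infer four stronger things that the documents do not support:

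- **That sites will keep these patients and score them as repairs.** This is inference. The sequence in Randomization points as much to removal.
- **That healing of a repair never made will be assessed.** Radiographic evaluation lists X-ray and MRI views and times but names no healing endpoint. Adverse event management speaks of healing after suturing only.
- **That the surgeon will choose the operation knowing the arm.** Blinding method says interveners are not blinded but does not identify them as the surgeon, and no section says the surgeon sees the allocation.
- **That uneven numbers between arms are bias.** With 10 such patients, a split of 7:3 or worse arises by chance with probability 2 × (120 + 45 + 10 + 1)/1024 = 352/1024 = 34% under simple allocation. That holds for any baseline trait present in 10 patients, and the test's error rate already allows for it.

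**Conclusion.** The point holds as an unresolved conflict between sections, made worse by the stated order of allocation and eligibility. Its size cannot be known from the article. The power figures depend on assumed shares of 5% to 30%. The removed case also assumes that these exclusions are not absorbed by the 20% loss allowance; if they were, the loss of power would be smaller. The kept case assumes no treatment difference in these patients.

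Because randomisation balances the mix on average, keeping these patients does not by itself bias the comparison. What suffers is the match to the stated population, the interpretation of results under a repair plan and repair-based return-to-play standards, and power. Selection bias becomes possible only if patients are excluded by someone who knows their arm, which the stated order permits. It should be fixed, but it does not invalidate the trial.

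**What to change.** Reconcile Study design, Randomization, Subjects and Surgical procedure:

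1. State that only patients who meet the Subjects criteria at arthroscopy, with a suture repair done, are randomised.
2. Open the envelope only after the operation is complete and eligibility has been recorded.
3. Record whether partial meniscectomy was added to the repair, and describe it by arm.

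This concerns eligibility and the timing of allocation. It takes no view on which operation any patient should have.

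Later allocation is workable because both arms' rehabilitation begins after surgery and the preoperative assessment is common to both. The cost is protocol wording, a later moment for opening envelopes, arm-specific software teaching moved to after surgery, and some consented patients who are never randomised. To randomise 2 × 32 = 64 patients, 64/(1 − f) must be consented if non-repairability is the only reason for loss: 68 at an assumed 5%, 72 at 10%, 80 at 20% and 92 at 30%.

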#### Postoperative rehabilitation protocol

A standardized postoperative rehabilitation protocol will be adopted according to the clinical guidelines in the American Academy of Orthopaedic Surgeons (AAOS) postoperative rehabilitation manual18 and previous studies1,2,4,14 (Table 1). [1, 2, 4, 18, 22]

#### Experimental group

Patients will receive daily exercise plans via a software platform for 12 weeks. This software can be installed on the patients' smartphones. Once the patient initiates the digital therapy platform, the system will utilize the smartphone's camera to capture the patient's position in real time (Fig. 2). As the patient performs the physical therapy exercises, the system will provide demonstration videos, verbal and auditory feedback on the patient's exercise posture and duration. The digital platform will also record the patient's exercise frequency and duration. This data will then be transmitted to the software platform for detailed analysis by the research team.

**Fig. 2 Fig2:**
[figure not shown]
The camera system

#### Smartphone camera requirements

It is recommended to have a photo resolution of 1280 × 720 pixels or higher and a video frame rate of 30 frames per second or higher for the smartphone camera.

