### Blinding method

For this study, blinding of the interveners and patients was not feasible. Blinding should be applied to the data collectors, data analysts, and outcome assessors in the study.

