#### Control group

Patients will be referred to the clinic weekly for 12 weeks postoperatively, during which they will receive instructions on physical therapy exercises. Every week, patients will learn the exercises at the clinic and will then be asked to take the instruction sheet home to complete the remaining exercises.

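### Only the digital arm depends on the patient's own smartphone, yet no listed criterion asks for a usable one before allocation, so phone-related losses could arise in that arm alone

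*Protocol article*

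**What the plan says.** All references are to the protocol article.

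- **Experimental group.** "Patients will receive daily exercise plans via a software platform for 12 weeks". The device is the patient's own: "This software can be installed on the patients' smartphones". The camera is integral, because "the system will utilize the smartphone's camera to capture the patient's position in real time". No loan device or fallback is described.
- **Smartphone camera requirements.** Despite the heading, the text is advisory: "It is recommended to have a photo resolution of 1280 × 720 pixels or higher", with a frame rate of 30 per second or more. It does not say what happens if a phone falls short.
- **Control group.** No phone is needed for the exercises: "patients will learn the exercises at the clinic and will then be asked to take the instruction sheet home".
- **Subjects.** There are five inclusion and four exclusion criteria. None mentions a phone, a camera or use of the software. The nearest is general: "Willing to participate in this clinical trial and receive follow-up".
- **Randomization.** Envelopes are opened in order of inclusion, which fixes the group. They then pass to the study implementer, "who will then use inclusion and exclusion criteria to decide whether each patient can be included in the study".
- **Blinding method.** "blinding of the interveners and patients was not feasible".

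**The concern.** Three features act together. One arm has a hardware need that the other lacks, the entry criteria do not apply that need to everyone, and inclusion is decided once the assignment can be known. A patient without a usable phone meets every listed criterion. If drawn to control, that patient proceeds normally. If drawn to the digital arm, the same patient may be unable to start, or may be left out by someone able to know the allocation.

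Two consequences would follow. If such patients are kept and analysed as allocated, the estimated effect is diluted. If they are dropped, the digital arm becomes selected on phone access while the control arm does not, and the comparison is no longer fully protected by randomisation. Feasibility is also part of the primary objective (Aim of study). A feasibility rate needs a clear denominator, and the article does not fix whether patients who cannot run the program belong in it.

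**Working it through.** **Inputs from the Sample size section:** d = 0.8, alpha = 0.05 (sidedness not stated), power 0.8, minimum 26 per group, 20% loss or exit, at most 32 recruited per group.

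**Step 1: the plan's own figures.** A two-sided two-sample t test with d = 0.8 and power 0.80 needs 25.52 per group, rounded up to 26. A one-sided normal approximation gives 20, so the plan's figure is two-sided. At 26 per group the noncentrality is d × √(n/2) = 0.8 × √13 = 2.88 on 50 degrees of freedom, and power is 0.807. The 32 reproduces as 26 × 1.2 = 31.2, rounded up. Dividing instead, 26/0.8 = 32.5, gives 33, one more per group. Neither figure is disputed here.

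**Step 2: an assumed phone-related loss.** Let q be the share of the digital arm that cannot start for want of a usable phone. The documents give no value, so q is varied. Assume that these patients gain nothing over control, that the standard deviation is unchanged, and that all patients are analysed as allocated. The effect becomes 0.8 × (1 − q).

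| q | diluted d | power, 26 per group | power, 32 per group |
|---|---|---|---|
| 0 | 0.80 | 0.81 | 0.88 |
| 10% | 0.72 | 0.72 | 0.81 |
| 20% | 0.64 | 0.62 | 0.71 |

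The 26 column describes a trial that has already used its whole allowance for loss. The 32 column describes one in which everyone recruited is analysed. In patients, 10% and 20% of 32 are about 3 and 6.

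**Step 3: the same patients dropped from the digital arm only.** Starting from 26 per group, the digital arm falls to 26 × 0.9 = 23.4 or 26 × 0.8 = 20.8 patients on average, against 26 in control. At d = 0.8 the power is 0.785 or 0.758. Little power is lost in this case. The cost is a one-sided removal on a patient characteristic, which no power figure captures.

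**Step 4: the sections side by side.** Subjects contains no device criterion, so applying it as listed removes nobody for lack of a phone. Randomization places that check after the envelope is opened, with an implementer who can know the arm. The article therefore contains no rule that would make a phone-related decision the same in both arms, and none that requires it before allocation.

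**The case against.** The strongest reply is that nothing shows this will happen. The Introduction treats smartphones as easy to come by. The camera figures are only recommended, so a weaker phone does not in itself disqualify a patient. The Compliance section provides software education before the trial, with handouts, reminders and support during it. Consent precedes randomisation, so a patient without a phone could decline. The printed criteria may also be abridged: the Aim of study speaks of adults, but no age limit is listed.

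Much of this stands. A reader might infer that non-starters or exclusions *will* fall in one arm only. The documents do not support that. They give no rate of unusable phones and no rule removing such patients. Nor is failure to start confined to the digital arm in general, because control patients can miss weekly visits and the Introduction itself cites long journeys and reduced compliance. Only the phone-related part is one-sided. The training also answers most of the worry about digital skill, though not about hardware.

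It can also be argued that randomising without a phone screen, and counting who cannot use the program, is a defensible pragmatic test of feasibility. That is a fair design choice, but it should be a stated one.

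What remains is more than omitted detail. The article sets out its criteria, gives the camera its own section, and states explicitly that eligibility is judged after the envelope is opened.

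**Conclusion.** The point holds as a risk. As the article stands, a patient unable to run the program can be randomised, and a non-start or exclusion for that reason could arise only in the digital arm. Its likely frequency is unknown and may be low.

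The power figures are illustrations, resting on assumed rates of 10% and 20%, no benefit in non-starters and analysis as allocated. Under those assumptions power lies between 0.62 and 0.72 at 26 per group, and between 0.71 and 0.81 at 32. The possible loss of comparability if patients are dropped after allocation depends on conduct that the article neither prescribes nor rules out. The change is worth making because it is cheap beforehand, whereas a one-sided loss cannot be repaired after randomisation.

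**What to change.** 1. In Randomization, complete all eligibility checks, including those made at arthroscopy, before the envelope is opened.
2. In Subjects, add one criterion for every patient whichever arm follows: access to a smartphone able to run the program. Use the recommended camera resolution and frame rate as the reference. Rely on the training already planned under Compliance, and do not add an exclusion for digital skill.
3. Record how many patients are screened out for lack of a suitable phone, and report that count beside the feasibility result.
4. Analyse all randomised patients in the arm to which they were allocated.

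The cost is one eligibility line, one screening-log field and a reordering of steps. The sample size figures do not change. The downside is a slightly narrower population, and feasibility among those randomised will look somewhat better than it would without the screen. The screening count must therefore always be reported with it.
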